## Abstract

**Summary:**

The aim of this study is to produce an easy to use checklist for general practitioners to complete whenever a woman aged over 65 years with back pain seeks healthcare. This checklist will produce a binary output to determine if the patient should have a radiograph to diagnose vertebral fracture.

**Purpose:**

People with osteoporotic vertebral fractures are important to be identified as they are at relatively high risk of further fractures. Despite this, less than a third of people with osteoporotic vertebral fractures come to clinical attention due to various reasons including lack of clear triggers to identify who should have diagnostic spinal radiographs. This study aims to produce and evaluate a novel screening tool (Vfrac) for use in older women presenting with back pain in primary care based on clinical triggers and predictors identified previously. This tool will generate a binary output to determine if a radiograph is required.

**Methods:**

The Vfrac study is a two-site, pragmatic, observational cohort study recruiting 1633 women aged over 65 years with self-reported back pain. Participants will be recruited from primary care in two sites. The Vfrac study will use data from two self-completed questionnaires, a simple physical examination, a lateral thoracic and lateral lumbar radiograph and information contained in medical records.

**Results:**

The primary objective is to develop an easy-to-use clinical screening tool for identifying older women who are likely to have vertebral fractures.

**Conclusions:**

This article describes the protocol of the Vfrac study; ISRCTN16550671.

## Background and rationale

Osteoporosis is estimated to affect 200 million women worldwide [1]. Osteoporotic fractures are strongly associated with morbidity, especially in terms of pain and disability: out of the people who have had a fracture, 42% have chronic pain and 33% of these describe the pain as severe or unbearable [2]. People who are hospitalised after a vertebral fracture (VF) have a higher mortality rate following fracture than those hospitalised after a hip fracture [3]. Unlike mortality following a hip fracture, mortality after a VF rises progressively after the event [3]. However, unlike hip fractures, most VFs do not require hospitalisation. Furthermore, the socioeconomic burden of VF is not as well defined as that of hip fractures, in part because the epidemiology of VFs is less well established as there is no universally accepted definition.

Only 25% of VFs result from falls, with the majority caused by daily activities such as bending forwards, climbing stairs or lifting objects [4]. People with VFs have a reduced health-related quality of life that is not solely a result of confounding by age, nor can it be fully explained by the presence of pain [5]. VF in older people has an effect on everyday activities such as reducing their ability to get in and out of a car, lift objects from the floor, walk a few blocks, climb up and down steps, reach or extend their arms above shoulder level, prepare meals and do the shopping [6]. VFs can also deprive people of their social support because their physical and functional capabilities have been limited [7]. The presence of VFs increases the risk of subsequent fractures, especially further vertebral or hip fractures [8], although there are medications available to reduce this risk [9–11]. Despite this, less than a third of people with osteoporotic VFs come to clinical attention [12] due to a variety of reasons including lack of clear clinical triggers to identify who should have diagnostic spinal radiographs.

We previously carried out a cross-sectional study of 509 older women from primary care, identifying four clinical triggers that could be combined in a simple tool to determine who should have spinal radiographs to identify undiagnosed osteoporotic VFs: height loss, back pain, previous fracture as an adult and rib-to-pelvis distance [13]. A cutoff from the regression equation was subsequently selected which identified all women with more than one VF and half of those with one VF. A large randomised controlled trial (RCT) of this screening tool, Cohort for skeletal health in Bristol and Avon (COSHIBA), was then undertaken in a primary care population of unselected women aged over 65 years [14]; 3200 women were recruited. Allocation to the screening arm approximately doubled the prescription of osteoporosis medications at 6 months follow-up. However, preliminary cost-effectiveness modelling suggested a cost-per-QALY of £30,000, making it unlikely that this would be cost-effective from the National Health Service (NHS) perspective in this setting, in the UK. This was mainly because of a low prevalence of VFs in this unselected population. A key finding from the National Osteoporosis Society into the realities of life with osteoporosis was that 58% of people with VFs have long-term back pain [15]. Therefore, we carried out a case-control study to look more specifically at the population of women aged over 60 years with back pain [16] to identify self-reported characteristics of pain that might help predict who has osteoporotic VFs. This study identified novel independent predictors of VF including shorter duration of back pain, pain described as crushing, pain improving on lying down and pain not spreading down the legs. Area under the curve (AUC) statistics for the combination of these factors to identify women with VFs was 0.85 (95%CI 0.79 to 0.92). Therefore, self-reported pain descriptives may identify people with back pain who have a vertebral fracture [16–18]. The Vfrac study combines the original COSHIBA screening tool with the newly identified pain descriptors (McGill questionnaire and new qualitative focus group work). Only women over 65 years with self-reported back pain will be eligible for this study. The aim of Vfrac is to produce and evaluate an improved screening tool (Vfrac) for use in older people presenting to primary care with back pain.

### The need for this study

The National Institute for Health and Care Excellence (NICE) guidelines CG146 [19] state the requirement for a study based in primary care to assess which people are at high risk of fracture. The Arthritis Research UK metabolic bone disease musculoskeletal trauma clinical studies group strategy suggested studies of new methods of detection of vertebral fractures and their effects on quality of life as one of their five focuses [20]. Furthermore, patients with osteoporosis and fracture identified earlier identification of osteoporosis as a top 2 research priority in a UK study of 1188 patients [21].

If Vfrac is deemed to be cost-effective, national implementation of Vfrac in primary care and local Fracture Liaison Services is likely to identify more of the currently undiagnosed older women with osteoporotic VFs, who have one of the highest risks of future fracture [22, 23], and will allow reduction in future fracture risk by approximately 50% after intervention [24].

### Primary aim

The aim of this Arthritis Research UK funded study (ref: 21507) is to produce and evaluate an improved tool (Vfrac) to screen older women with back pain for osteoporotic vertebral fractures.

## Design and methods

### Outline

The Vfrac study is a multicentre, pragmatic, observational cohort study with data collection at baseline and 3 months follow-up. Baseline data collection is by self-report, physical examination at a research clinic plus spinal radiographs. Data collection at follow-up is by self-report and from GP electronic records. Table 1 shows the timeline for the study.

**Table 1 Tab1:** Vfrac study timeline

	2017	2018				2019				2020				2021	
	Pre-funding	Jan–Mar	Apr–Jun	Jul–Sep	Oct–Dec	Jan–Mar	Apr–Jun	Jul–Sep	Oct–Dec	Jan–Mar	Apr–Jun	Jul–Sep	Oct–Dec	Jan–Mar	Apr–Jun
Ethics, research governance and other approvals; staff recruitment	●	●	●												
Recruitment of general practices			●		●		●								
Recruitment of patients				●	●	●	●	●	●	●					
Data collection: self-report (baseline questionnaire) and physical examination				●	●	●	●	●	●						
Spinal radiographs				●	●	●	●	●	●	●					
Statistical analysis												●	●		
Generate web-based Vfrac tool													●	●	
Identification of stopping rules for future definitive trial													●	●	
Follow-up of patients having X-rays (follow-up questionnaire and medical records download)					●	●	●	●	●	●	●				
Modelling cost-effectiveness													●	●	●
Dissemination, and preparation of future pilot application			●								●		●	●	●

A total of 1633 women aged over 65 years will be recruited via primary care from two sites within England — Bristol and Stoke-on-Trent. Potential participants will be asked for their consent via post and asked to fill in a baseline questionnaire containing items on demographics, socioeconomic status, traditional risk factors for osteoporosis, back pain, quality of life, medication use, healthcare utilisation and comorbidity. Upon the study team’s receipt of the completed baseline questionnaire and consent form, an appointment will be made for the participant to have a physical examination in secondary care followed by a lateral thoracic and lateral lumbar radiographs performed using standard NHS standard operating procedure on the same day. Before the physical examination, the participant will be asked, in person, to sign another consent form. In this consent process, they will be asked if they agree to the physical examination and radiograph. The radiograph report will be sent to the participant’s general practitioner (GP) as if the GP had ordered the radiograph. The GP practices will be given a guidance document upon recruitment, providing information on recommended pathway for patients with a vertebral fracture. This advice has been taken from the North Bristol NHS Trust guidance for GP practices within BSSG CCG (Fig. 1). The first step in this guidance is an X-ray to confirm VF.

**Fig. 1 Fig1:**
[figure not shown]
Management of a patient with an osteoporotic vertebral fracture. Note: (Manage patients according to this pathway provided they have no recent history of significant back trauma, no red-flag clinical features to suggest alternative diagnoses such as malignancy and are at risk of osteoporosis (e.g. FRAX score amber or red—see http://www.shef.ac.uk/FRAX/tool.jsp)

A copy of the radiograph and the report will also be sent to the chief investigator for research analysis after identifying information has been removed. Three months after the radiograph, the participant will be asked to complete a follow-up questionnaire, containing questions about whether results of the spinal radiograph were communicated to the patient, whether they started on any new medication, and whether they have been referred to any healthcare service, e.g. physiotherapy and quality of life. Data collection from the participants’ GP electronic records will also be conducted at this time. This will comprise extraction of information about current medication, number of contacts with healthcare practitioners, whether results of the radiograph are recorded in the notes and concomitant illnesses. The end of study will be the date of receipt of the last follow-up questionnaire of the last patient. The study flowchart is provided in Fig. 2.

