**Fig. 2 Fig2:**
[figure not shown]
Study flowchart

The primary objective is to develop a clinical screening tool for identifying older women with back pain who are likely to have VF. The output will be a simple clinical checklist of self-reported data and data from the physical examination which will produce a binary assessment of (1) yes—this person needs a spinal radiograph, or (2) no radiograph needed. The primary evaluative measure will be the accuracy of the Vfrac tool as represented by the sensitivity and specificity of > 80%.

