## Data collection and analysis

Data collection will occur at baseline via self-report, a physical examination at a research clinic and spinal radiograph, and at follow-up via self-report and through GP electronic records.

The items in the questionnaires were chosen based on literature review and previously published work [13, 14, 16]. The questionnaires will contain the following items:Margolis pain diagrams [25] at baselinePHQ-9 [26] at baseline and follow-upPainDETECT [27] at baselineFRAX [28] clinical risk factors only at baselineQ-Fracture [29] at baselineDiagnosis of osteoporosis at baseline and follow-up (‘have you ever been diagnosed with osteoporosis (brittle bones)?’; ‘approximate date of diagnosis’)Traditional risk factors of osteoporosis at baselineEQ5D-5L [30] at baseline and follow-upICECAP-O [31] at baseline and follow-upItems based on focus group work with patients with VFs and based on the McGill Pain questionnaire [16, 18] at baselineDescriptions of pain deemed important during focus group work (REC reference number16/NS/0110) at baselineUse of pain medication at baseline and follow-upCurrent prescription drugs and over the counter medication/remedies/supplements at baseline and follow-upUse of healthcare services at baseline and follow-upWhether results of the radiograph were communicated to the patient at follow-up

During the research clinic, the following information will be collected: height (stand-alone stadiometer), weight, chest expansion, rib-to-pelvis distance, wall-tragus distance and waist circumference. To calculate height loss, we will be relying on the participant to know how tall they were at 25 years. In the baseline questionnaire, the participants are asked ‘how tall were you at aged 25?’ and ‘how tall are you now?’. These data were chosen based on literature review and previous published research [13, 14, 16]. The Vfrac study chief investigator will have access to all spinal radiographs with the study ID number as the only identifying feature.

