### Analysis of outcome measures—vertebral fractures

All spinal radiographs will be analysed by a trained clinician researcher for the presence of VFs using the Algorithm-Based Qualitative (ABQ) approach [32]. Images that are difficult to interpret via the ABQ method or using automated QM will be viewed by the trained clinician researcher [name] and a spinal radiologist and consensus reached. In ABQ, the diagnosis of osteoporotic fracture assumes that these fractures always involve the endplate within the vertebral ring. This method recognises that short vertebral height is not always due to fracture [33], but may be developmental or degenerative in origin. As such, the ABQ is felt to be more specific for true VF, particularly mild deformities and avoids the high false-positive rate of quantitative morphometry (QM) [34]. In addition, QM [35] will also be used to identify VFs as this method is available within automated software for the analysis of spinal radiographs and has the potential to become more commonly used within the NHS. However, QM is less specific and is associated with an increased number of false positives.

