### Analysis—developing the clinical tool

Data from the questionnaires and physical examination will be linked to those from the analysis of spinal radiographs for the presence/absence of vertebral fractures. The first step will be univariable analyses to identify associations between risk factors and presence of VFs. Multiple logistic regression analyses will be performed with the aim of identifying clinical risk factors that are independently predictive of the presence of VF. All likely contenders from the univariable analysis will be included, with variables deleted in a backwards fashion whilst considering aspects such as clinical interpretation and associations between the variables, rather than relying on a simple automated basis. For example, once a final model is obtained, all deleted variables will be checked one by one to confirm if they did not contribute further. Hence, the number of variables to be considered in the multivariable modelling has not been pre-specified (on, for instance, an events per variable threshold), but the analyses will be structured, including considering variables in cognate groups, so that it is unlikely that any one model will involve more than 6–10 variables [36]. Separate analyses will then be performed to identify a cutoff to predict one or more VFs and more than one VF. Sensitivity and specificity of the pre-determined threshold will be calculated using standard techniques, comparing against the gold standard of identification of VFs from radiographs by the chief investigator using the ABQ method.

Secondary analyses will involve calculating the AUC to measure discriminative ability. To provide an estimate of the validity of the predictive models, 200 bootstrap samples of the original dataset will be derived (each bootstrap sample will be generated by randomly sampling from the original dataset with replacement 505 times). Logistic regression will then be performed on each bootstrap sample using the same set of predictor variables as in the final model, and the regression coefficients and AUC calculated. Each set of bootstrap sample coefficients will then be used to calculate AUC for the original dataset. The difference between these estimates will be used to evaluate the extent to which the discriminative ability of our final model decreases when applied to other random samples [37].

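### The routine radiology report is sent, with the image, to the reader who sets the gold standard, so the ABQ reference is not protected from anchoring to it

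*Protocol article*

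**What the plan says.** The Outline describes two destinations for the radiology report.

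- The first is clinical: "The radiograph report will be sent to the participant’s general practitioner (GP) as if the GP had ordered the radiograph".
- The second is for research: "A copy of the radiograph and the report will also be sent to the chief investigator for research analysis", with identifiers stripped first.

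The section on developing the clinical tool measures sensitivity and specificity against the "gold standard of identification of VFs from radiographs by the chief investigator using the ABQ method". The section on vertebral fracture outcomes describes the same reading under another role: "All spinal radiographs will be analysed by a trained clinician researcher for the presence of VFs using the Algorithm-Based Qualitative (ABQ) approach". Images that are hard to interpret are viewed by that researcher "and a spinal radiologist and consensus reached". Neither section gives the routine report a role in the reading.

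The data collection section adds one statement of a masking kind: "The Vfrac study chief investigator will have access to all spinal radiographs with the study ID number as the only identifying feature".

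**The concern.** The person who fixes the reference standard receives, in the same transfer and for a stated research purpose, another reader's conclusion on the same film. De-identification does nothing about that conclusion.

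The article chooses ABQ because it is held to be more specific than quantitative morphometry, above all for mild deformities, and it sends difficult images to a defined consensus. A routine report that is visible at reading would add a further opinion outside that process, and the article does not say that the report was made by ABQ.

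Every accuracy figure for Vfrac is computed against this reference. Sensitivity and specificity above 80% are the bar for going on to a definitive trial, so a reference that drifts towards a different reading can affect that decision.

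**Working it through.** **1. The file flow.** Set side by side, the sections give this sequence:

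| Step | Protocol article | Content |
|---|---|---|
| Report to the GP | Outline | Routine report, for care |
| Image and report to the chief investigator | Outline | For research analysis, identifiers removed |
| Images held under study ID | Data collection and analysis | Identity hidden |
| Gold standard set | Analysis, developing the clinical tool | Chief investigator, ABQ, from radiographs |

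No step withholds the report until the ABQ result is recorded. The transfer is stated, so the point does not rest on silence alone.

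**2. The plan's own figure.** The inputs from the Sample size section are sensitivity 85%, prevalence 12% and a 95% half-width of 5 points.

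N = 1.96² × 0.85 × 0.15 / 0.05² / 0.12 = 195.9 / 0.12 = 1633.

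This reproduces the planned size, which this point does not dispute. It implies about 196 women with a fracture and 1437 without.

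**3. How sensitive the primary measure is to reference error.** Assumptions, not taken from the documents: true Se = Sp = 0.85, and reference errors independent of the tool's result. Let p be prevalence, f the share of women without fracture who are over-called, and m the share of fractures missed.

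*Over-calling only:* apparent Se = [p·Se + (1−p)·f·(1−Sp)] / [p + (1−p)·f]

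- p = 12%, f = 2%: (0.1020 + 0.00264) / 0.1376 = 76.0%
- p = 12%, f = 5%: 66.2%
- p = 20%, f = 2%: (0.1700 + 0.0024) / 0.2160 = 79.8%
- p = 20%, f = 5%: 73.3%

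Break-even at p = 12%, with x women over-called: (0.85 × 196 + 0.15x) / (196 + x) = 0.80 gives x = 9.8 / 0.65 ≈ 15. That is about 1% of the 1437 women without fracture.

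*Misses only:* apparent Sp = [p·m·(1−Se) + (1−p)·Sp] / [1 − p·(1−m)]

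- p = 12%, m = 10% to 30%: 84.1% to 82.2%
- p = 20%, m = 10% to 30%: 83.3% to 80.1%

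Starting from 85%, specificity stays above 80% in these cases. It crosses only if the true value is nearer the bar. With an assumed true Sp of 81%, p = 20% and m = 10%: (0.003 + 0.648) / 0.82 = 79.4%.

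**4. Direction.** If the report adds such errors to the ABQ reading, apparent accuracy falls. If it removes errors that a masked reading would have made, apparent accuracy rises: taking away the 2% over-calling above moves sensitivity from 76.0% back to 85%. Errors related to the tool's result could act either way. The documents give no means of choosing between these cases.

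**The case against.** The strongest reply is that being sent a report is not the same as reading from it. The analysis section says that fractures are identified from radiographs, and the report may be wanted for objective 3, which follows what happened after the radiograph. Reading order is also a detail that a condensed article may leave to a full protocol or reading manual. This stands as far as it goes. A reader might infer that the gold standard is in fact not independent, but the article does not show that. The reply does not remove the point, because the article does describe the transfer, its content and its masking step, and the content includes the report.

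Three further objections hold:

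- A reader might infer that the index test is built into the reference. It is not. The tool is described thus: "The output will be a simple clinical checklist of self-reported data and data from the physical examination". The report is not an input.
- The timeline places statistical analysis from July–September 2020, after radiographs end in January–March 2020. If reading follows acquisition, the reader cannot know the tool's result.
- A reader might infer a bias that favours the tool, with fractures the tool misses being read as normal more often than those it finds. That needs errors linked to the tool's result. The article gives no tool performance by fracture severity that would support it.

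The outcome section also calls the reader a trained clinician researcher, so the identification with the chief investigator rests on the analysis section.

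**Conclusion.** The point holds in a limited form. The person named as setting the gold standard receives the routine report with the image for research analysis, and the only stated safeguard removes identity. The independence of the ABQ reference is unprotected; it is not shown to be lost.

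The size and direction of any effect cannot be computed from the documents. The figures above rest on assumed accuracy, assumed error rates and errors unrelated to the tool. They show only that reference errors of 1% to 2% among women without fracture are enough to move apparent sensitivity across the 80% target. Specificity is less easily moved unless its true value lies close to 80%. The sample size is not affected.

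**What to change.** Send only the image labelled with the study ID for ABQ reading. Record and lock the ABQ result, including consensus reads with the spinal radiologist, masked to the routine report. Release the report to the research team only after that, for the follow-up and pathway analyses. State this sequence where the transfer is described and where the gold standard is defined.

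The cost is a change in the order of file release, with no extra reader, procedure or participant. If this is already the practice, one sentence saying so settles the point.
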